### Harms

2.17

To evaluate the safety, both the pharmacopuncture and PT groups will undergo blood test (white blood cell, neutrophil, lymphocyte, monocyte, eosinophil, basophil, red blood cell, hemoglobin, hematocrit, mean corpuscular volume, mean corpuscular hemoglobin, mean corpuscular hemoglobin concentration, platelet, erythrocyte sedimentation rate, total protein, albumin, total bilirubin, alkaline phosphatase, aspartate aminotransferase, alanine aminotransferase, gamma-glutamyl transpeptidase, and C-reactive protein) before treatments initiation and after the last treatment. The collected blood samples will be discarded immediately after analyzing the results. Matters pertinent to biological samples disposal will adhere to the SOP presented by the medical laboratory team. All adverse events reported during the study period will be collected, and the percentage of patients who develop an adverse event will be calculated for each group. The incidence of adverse event in the 2 groups would then be compared using the Chi-squared test or Fisher exact test.

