### Adverse events

2.8

For safety assessment, white blood cell, neutrophil, lymphocyte, monocyte, eosinophil, basophil, red blood cell, hemoglobin, hematocrit, mean corpuscular volume, mean corpuscular hemoglobin, mean corpuscular hemoglobin concentration, platelet, erythrocyte sedimentation rate, total protein, albumin, total bilirubin, alkaline phosphatase, aspartate aminotransferase, alanine aminotransferase, gamma-glutamyl transpeptidase, and C-reactive protein will be performed before the start and after the end of treatment sessions in both study groups to compare the incidence of adverse events between groups.

An adverse event refers to undesirable and unintended signs, symptoms, or diseases that would occur after a procedure. It includes responses that are not directly related to the procedure. In the present study, we will collect data on adverse events based on the patients’ reports of symptoms and our observations. We will then analyze the incidence of adverse events that are suspected to be related to the treatment. This would include abnormal laboratory results and serious adverse events. The causality between the treatment and the adverse events will be assessed based on a 6-point scale, following the world health organization-Uppsala monitoring center causality assessment system (1 = definitely related, 2 = probably related, 3 = possibly related, 4 = probably not related, 5 = definitely not related, and 6 = unknown). The severity of all adverse events will be classified into 3 levels following the Spilker classifications:

(1)Mild, does not need treatment or does not significantly impair daily activities (functions)(2)Moderate, significantly impairs daily activities (functions) and may require treatment but resolves afterward(3)Severe, a serious adverse event that requires intensive treatment and leaves sequelae.

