### Sample size calculation

2.9

The null hypothesis of this study is that there will be no difference in the outcomes between the experimental and control groups when treating chronic neck pain. The hypothesis will be tested using analysis of covariance (ANCOVA) as the primary analytical test. The significance level will be set to α = 0.05 (2-tailed), with type 2 error (β) of 0.2 and a power of 80%. The sample required size was calculated based on a meta-analysis that had analyzed the effectiveness of pharmacopuncture compared to acupuncture or electropuncture therapy in patients with cervical spondylosis.^[12]^ Although the control group of this study differs from ours, we determined that we can utilize that study for sample size calculation based on their findings that the effectiveness of acupuncture in treating neck pain is equivalent^[21]^ or superior^[21,22]^ to that of PT. The mean difference in VAS between the pharmacopuncture and control groups based on this meta-analysis was 1.79 ± 2.74.^[12]^ When effect size is calculated based on this, the f-value is 0.33. Using the G∗Power software, version 3.1.9.4 (Franz Faul, Christian-Albrechts-Universität Kiel, Kiel, Germany), a total of 77 participants will be required. Assuming a withdrawal rate of 20%, we plan to recruit 100 participants.

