### Randomization and allocation concealment

2.11

A statistical expert will randomize an equal number of patients (n = 50, each) into 2 groups, using a random table generated by the nQuery Advisor (Statistical Solutions Ltd., Cork, Ireland) 7.0 (or SAS 9.0 (SAS institute, Cary, USA) or SPSS 21.0 (SPSS Inc., Chicago, USA)) software. The randomization results will be delivered to each institution in sealed opaque envelopes to be stored in a double-locked cabinet. The investigator will provide an adequate explanation of the trial, and each patient that meet the inclusion and exclusion criteria and voluntarily sign the consent form will open a randomization envelope to be randomly assigned a subject number. The investigator will record the assigned random number for each patient on the patient's electronic chart.

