### Statistical methods

2.14

Sociodemographic characteristics and treatment expectancy will be evaluated for each group. Continuous variables will be expressed as mean (standard deviation) or median (quartiles). Differences between the 2 groups will be analyzed using the Student *t* test. Categorical variables will be expressed as frequency (%) and will be analyzed using the Chi-squared test or Fisher exact test.

The endpoint of this clinical trial is the differences in changes in the continuous outcomes (NRS, VAS, NDI, NPQ, EQ-5D-5L, SF-12) at each time point compared to the baseline between the 2 groups. As the primary analysis, ANCOVA will be performed with factors that significantly differ between the 2 groups at baseline as covariates and the groups as fixed factors. As an additional analysis, a linear mixed model will be used to analyze the differences in the changes between visits and the trend of such changes. The linear mixed model will be processed with the mixed model for repeated measures. In addition, the areas under the curve (AUC) will be calculated at each time point after randomization for each outcome during the treatment period and through the entire study period. The Student *t* test will be used to compare the difference in AUC between 2 groups. Additionally, percentages of patients whose NRS and VAS for neck pain decreased by more than 50% from the baseline will be compared for each time point. The time since randomization to the improvement of neck pain, as determined by a drop in the pain indices by more than 50%, will be estimated using the Kaplan–Meier survival analysis. The curves will be compared using the log-rank test. Furthermore, hazard ratios will be compared using the Cox proportional hazard model.

In this study, we will perform both intention-to-treat (ITT) and per-protocol analyses, with ITT analysis as the primary approach. For PP analysis, participants who underwent 6 or more treatment sessions during the 4-week treatment period will be analyzed separately. Missing data in the principal ANCOVA analysis and the AUC analysis will be processed by multiple imputation. Missing time point data in the survival analysis will be censored. All statistical analyses will be performed using the SAS version 9.4 statistical package (SAS Institute, Cary, USA), and differences will be considered statistically significant when *P* < .05.

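### Section 2.17 compares adverse events between arms only by a significance test, in a trial sized for VAS; a risk difference with a 95% interval would be a cheap improvement

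*Protocol article*

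**What the plan says.** Section 2.17 (Harms) collects all adverse events reported during the study, gives the percentage of patients affected in each group, and continues: "The incidence of adverse event in the 2 groups would then be compared using the Chi-squared test or Fisher exact test".

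Section 2.8 (Adverse events) adds blood tests before and after treatment in both groups, "to compare the incidence of adverse events between groups". It also plans an analysis of events suspected to be treatment-related, covering abnormal laboratory results and serious events, with causality and severity grading. It names no further method for comparing the arms.

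Section 2.14 (Statistical methods) sets one threshold for all analyses: "differences will be considered statistically significant when *P* < .05".

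The sample size in section 2.9 rests on VAS: "The mean difference in VAS between the pharmacopuncture and control groups based on this meta-analysis was 1.79 ± 2.74". The recruitment target follows from it: "Assuming a withdrawal rate of 20%, we plan to recruit 100 participants". Section 2.11 allocates 50 patients to each arm. The article states no expected adverse event rate, and no risk difference, interval or margin for harms.

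**The concern.** For harms, the costly mistake is to overlook a real excess. A test of no difference at the 5% level does not control that mistake, and nothing in section 2.9 sizes the trial for it. If the between-arm output is only significant or not significant, a non-significant result cannot separate the absence of an excess from an excess too small for this trial to see.

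This matters because the Discussion wants the results to inform clinical and policy decisions about an injected treatment. Section 2.15 plans no data monitoring committee and no interim analysis, so the end-of-trial comparison is the main randomised evidence on harms. An interval from the same counts would show how large an excess the data leave open.

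**Working it through.** **The plan's own figure.** From section 2.9, d = 1.79 / 2.74 = 0.653 and f = d / 2 = 0.327, stated as 0.33. With two-sided α = 0.05, 80% power and the noncentral F distribution (λ = N f²), f = 0.33 gives N = 75 and the unrounded f gives N = 76. The stated 77 is within two patients. Then 77 / (1 − 0.20) = 96.25, which rounds up to 97, and 100 are recruited. The figure is sound for VAS; no such calculation is given for adverse events.

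**Inputs for harms.** 50 per arm (section 2.11); rejection at P < .05 (section 2.14), taken as two-sided; chi-squared or Fisher test (section 2.17). The event rates are assumed, because the article gives none.

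**Approximate power, 10% v 20%.** The formula is

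power = Φ{ [ |p2 − p1| − 1.96 √(2 p̄(1 − p̄)/n) ] / √( p1(1 − p1)/n + p2(1 − p2)/n ) }

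- p̄ = 0.15, so √(2 × 0.15 × 0.85 / 50) = 0.0714, and 1.96 × 0.0714 = 0.1400
- denominator: √(0.0018 + 0.0032) = 0.0707
- power = Φ((0.1000 − 0.1400) / 0.0707) = Φ(−0.565) = 0.286, a miss rate of 71.4%

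**Exact power.** This sums the binomial probabilities of every pair of outcomes for which P < .05, at 50 per arm.

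| Assumed rates | Power, uncorrected chi-squared | Power, Fisher | Miss rate |
|---|---|---|---|
| 5% v 15% | 39% | 24% | 61% to 76% |
| 10% v 20% | 30.3% | 19.5% | 69.7% to 80.5% |
| 10% v 25% | 53% | 41% | 47% to 59% |
| 20% v 30% | 21% | 16% | 79% to 84% |
| 20% v 40% | 60% | 52% | 40% to 48% |
| 10% v 30% | 73% | 64% | 27% to 36% |
| 10% v 35% | 88% | 82% | 12% to 18% |

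By the normal approximation, 80% power for 10% v 20% would need 199 per arm.

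**What each output would show.** Suppose 10/50 and 5/50 patients have an event.

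- Chi-squared: z = 0.10 / 0.0714 = 1.40, P = 0.16. Fisher: P = 0.26. Both are reported as not significant.
- Newcombe interval, built from the Wilson limits of each arm (10/50: 0.112 to 0.330; 5/50: 0.044 to 0.214):
  - lower = 0.10 − √((0.200 − 0.112)² + (0.214 − 0.100)²) = −0.04
  - upper = 0.10 + √((0.330 − 0.200)² + (0.100 − 0.044)²) = +0.24

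The interval says that the data are compatible with anything from 4 points fewer to 24 points more. The P value does not show this. Against 5/50, significance needs 13/50 by chi-squared (P = 0.037) or 14/50 by Fisher (P = 0.040).

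**No events in an arm.** The exact upper limit for 0/50 is 1 − 0.025^(1/50) = 7.1%.

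**The case against.** The strongest reply is that nothing here is wrong. Chi-squared and Fisher tests are conventional and valid for two percentages. The trial's aim is comparative effectiveness, so it had no reason to be sized for adverse events, and low power for modest differences is usual with 100 patients. A full protocol or analysis plan, not shown, may add an interval. The percentages in each arm are already planned, and a reader could derive the interval from them. Most of this stands and keeps the severity low. What remains is that section 2.17 names a method instead of leaving it open, and a more informative one is available from the same counts.

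Stronger readings are tempting, and the article does not support them:

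- A reader might infer that the investigators will take P > .05 as showing comparable safety. The article never says so and plans no equivalence or non-inferiority claim on harms.
- A reader might infer that the trial is blind to harms. It is not: a very large excess such as 10% v 35% would probably be detected, and related and serious events are already to be analysed under section 2.8.
- A reader might say that a doubling from 10% to 20% is missed at least 70% of the time. The exact figure for the uncorrected chi-squared test is 69.7%, and the rates are assumed.
- A reader might use the 20% withdrawal allowance to lower the numbers further. That allowance belongs to the VAS calculation, and nothing says that withdrawn patients leave the adverse event denominator.

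**Conclusion.** The point holds as a low-severity improvement. The only between-arm method stated for harms is a significance test. Under assumed rates of 10% and 20%, with 50 per arm and a two-sided 5% level, it would miss the difference about 70% to 80% of the time, depending on which of the two named tests is used. The size depends wholly on the assumed rates. A non-significant result from this test would say little about modest excesses. The primary analysis and the sample size for VAS are unaffected.

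**What to change.** In section 2.17, state that the between-arm risk difference will be reported with its 95% confidence interval (Newcombe or exact) for any adverse event and for the treatment-related and serious events already planned in section 2.8. Where an arm has no events, give the exact upper limit (7.1% for 0/50). Base the safety statement on the interval, and keep the chi-squared or Fisher P value as a descriptive addition.

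The cost is one or two sentences and a few lines of SAS on data already collected, with no extra patients or procedures. The downside is that the interval will be wide and the safety statement less favourable than a bare non-significant result.

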### Auditing

2.18

Audit will be conducted at each trial site once during the trial by investigators independent from this study.

### Ethical approval

2.19

Before the start of the study, the study protocol, CRF, ICF, and patient recruitment announcement have been submitted to the IRB at each site and obtained approval for the study (JASENG June 06, 2019, JASENG June 10, 2019, JASENG June 11, 2019, and JASENG June 08, 2019). Any amendments to the protocol, CRF, ICF, or patient recruitment announcement will be made only upon IRB approval. All changes will be updated on the trial registries. All clinical investigators participating in this study will be educated about the Helsinki Declaration and the Korean Good Clinical Practice Guidelines, the study protocol, and the SOP to protect the patients participating in this study.

### Informed consent

2.20

Before the start of the clinical trial, investigators will provide the patients with an adequate explanation about the contents of this clinical trial and information about the treatments. The investigators would obtain a signed informed consent and provide a copy of the consent form to each participant. If personal information would need to be collected, such as a copy of a bankbook to receive the transportation reimbursement, we will explain this need to the patients and obtain their consent for collecting personal information.

### Confidentiality

2.21

All personal information of trial participants will be strictly managed under IRB supervision, and confidentiality of personal data will be strictly protected. All data collected from participants who consented to participate in this trial would be processed anonymously. If such data were to be disclosed to a third party for research purposes, arbitrary codes would be used with all personal identifying information removed.

### Ancillary and post-trial care

2.22

An emergency contact number will be provided to all trial participants to contact in case of questions, when experiencing medical problems, or a study-related symptom during the study period, so they can receive the necessary assistance. Any participant directly harmed in relation to the trial would be legible to receive appropriate medical care as determined by the investigator. Compensations for any damages would be processed per the designated trial-related insurance agreement.

## Discussion

3

Pragmatic clinical studies have been developed based on the perspective that the conventional explanatory trials do not produce appropriate clinical outcomes because they are optimized to determine efficacy. Highly trained investigators have conducted explanatory trials on relatively small sample size and strictly selected patient groups.^[24]^ Schwartz and Lellouch stated that explanatory trials are studies that test a physiological or clinical hypothesis. In contrast, pragmatic trials are studies that contribute to clinical decision or policy-making by providing evidence for selecting an intervention in a real-world practice.^[25]^ In other words, pragmatic trials have been designed to overcome the limitations of conventional clinical trials. Their significance is in determining treatment outcomes in real-world clinical settings. Notably, many Korean medicine trials are focused on verifying the effectiveness of clinically popular treatment or comparing their effectiveness with that of other treatments, as opposed to developing or aiming to obtain approval of novel drugs or medical technologies. Pragmatic clinical trial models are, therefore, more appropriate in studies related to Korean medicine.

A pragmatic-explanatory continuum indicator summary (PRECIS) is a tool with 10 domains that helps design clinical trials on a continuum from explanatory attitude (ideal situation) to a more pragmatic attitude (usual care).^[26]^ However, weaknesses have been highlighted: the absence of a rating scale, problems with some domains, need for better guidance, and lack of validation. The revised version of PRECIS, PRECIS-2, has 9 domains: eligibility criteria, recruitment, setting, organization, flexibility (delivery), flexibility (adherence), follow-up, primary outcome, and primary analysis, which scored from 1 (very explanatory) to 5 (very pragmatic).^[27]^

In this study, we will be recruiting a broad spectrum of patients with chronic neck pain, irrespective of imaging results, but only between the ages of 17 and 70 years. The eligibility criteria can, therefore, be given a score of 4. Recruitment is given a score of 4 as it will be utilizing means such as subway advertisements to approach a wider audience. The setting could be given a score of 3, as we will only be recruiting participants at 4 hospital-level healthcare institutions. The organization could be assigned a score of 5 for not relying on imaging equipment or assistance from other experts in the diagnosis and treatment of neck pain. Flexibility (delivery) could also be given a score of 5 because we will not be designating a specific treatment regimen for the physicians to follow. Rather, we will be providing data on the frequently used pharmacopuncture and PT regimens for an outpatient setting,^[9,13]^ and let the physicians autonomously choose, deliver, and chart the type and site of treatment within the confinements of their respective treatment group, which will be retrospectively analysed. Such clinical decisions will be made based on the patients’ symptoms and imaging results. Flexibility (adherence) could be given a score of 4. Although participants will not be dropped out based on a specific adherence criterion during the treatment period, we will recruit patients who can visit the facility for an adequate number of treatment sessions during the participant screening stage. Follow-up can be given a score of 2 because a variety of questionnaires will need to be completed during over-the-phone or in-person follow-up sessions at designated time points after the completion of treatment. This would require additional time and subject participation beyond the general treatment. The primary outcome domain could be given a score of 5, as the primary outcome of this study is VAS for neck pain. This primary outcome is directly related to the patient's symptoms and is an important outcome from the patient's perspective. The primary analysis could also be given a score of 5. We plan to perform ITT analysis using data from all participants, including those who showed noncompliance and those with values below the expected level. The PRECIS-2 wheel of this protocol is shown in Supplementary 1.

This protocol delineates a pragmatic RCT that aims to compare the effectiveness of pharmacopuncture, an intervention widely used in Korean medicine clinical practice, with that of the standard treatment. Our goal is to present evidence that would assist clinical decision and policy-making.

### Protocol version

3.1

The study protocol version is 1.5 (March 16, 2020). Important amendments to the study protocol or other changes hereafter will be periodically updated on the trial registration sites.

### Dissemination policy

3.2

The investigators will share the results of this study with the participants, healthcare professionals, and the public by publishing or through trial registries. Only investigators who were directly or indirectly involved in the study will be listed as authors on study-related publications.
